# Establishing a telemedical supported trans-sectoral collaboration network from community support to emergency care for outpatient care recipients: study protocol of a prospective non-randomized complex intervention study with a pragmatic approach, Stay@Home – Treat@Home

**DOI:** 10.1186/s12877-024-05553-6

**Published:** 2024-12-02

**Keywords:** Outpatient care recipients, Telemedicine, Digital interactive health diary, Trans-sectoral care, Study protocol

## Abstract

**Background:**

Demographic changes in Germany are increasing the number of outpatient care recipients, who often resort to emergency care due to difficulties accessing timely outpatient medical care. Previous studies suggest that early detection and telemedical interventions could reduce unnecessary hospitalizations. The new form of healthcare aims to provide continuous, flexible healthcare for outpatient care recipients using digital technologies to detect health deteriorations and facilitate interventions at home. The goal of our study is to evaluate, whether the number of emergency situations and hospital stays will be reduced, and health outcomes will be improved compared to standard care.

**Methods:**

In this prospective non-randomized complex intervention study with a pragmatic approach, we aim to evaluate a new form of healthcare focused on establishing an interdisciplinary network for outpatient care in the homes of care-dependent individuals. Utilizing a digital interactive health diary, health data will be gathered from participants, caregivers, and healthcare providers, covering both stable primary care and acute situations. A telemedical network will coordinate measures, including non-medical aid, nursing care, and medical assistance. A total of 1,500 participants will be recruited for the intervention group, matched with a control group from health insurance data. A second control group with n=300 will provide self-reported measures. The study is planned to span eight quarters, with data collected from the digital interactive health diary and health insurance records. Evaluation perspectives include health insurance, patients, and healthcare providers, assessing utilization and costs compared to standard care, health status, health-related quality of life, care dependency, interdisciplinary cooperation, and usability of the new technology.

**Discussion:**

Demographic change results in a larger older people population, exacerbating mobility issues and care dependency, worsened by the shortage of medical personnel. Stay@Home – Treat@Home aims to enable home health monitoring and care, reducing hospitalizations. The digital interactive health diary supports direct communication, allows remote monitoring, and empowers patients and caregivers to manage health changes. Nursing aid personnel and physicians can access entries for informed interventions. The development of the digital interactive health diary aims to improve the situation of care-dependent individuals. Evaluating its effectiveness and efficiency is crucial for the development and implementation of new technologies.

**Trial registration:**

German Clinical Trials Register, ID: DRKS00034260, registered on May 14, 2024 (retrospectively registered): https://drks.de/search/de/trial/DRKS00034260 and https://who.int/clinical-trials-registry-platform/network/who-data-set.

## Introduction

### Background

Due to demographic changes, the number of outpatient care recipients is increasing nationwide in Germany. In the year 2050, approximately one in ten people in certain regions of Germany will be dependent on care [1]. Four out of five are cared for at home, and more than half of them is 80 years or older [2]. People who require care often experience impairment in their health and mobility [3]. As a result, they require regular medical supervision but face greater challenges in accessing outpatient medical care, particularly specialist medical services [2]. Another area of concern is the critical use of medication. Every 7th person in need of care receives a prescription for medication with associated risks. Additionally, polypharmacy is often a result of uncoordinated healthcare and more common among those in need of care, posing a risk of adverse drug interactions [2].

Consequently, people who are care dependent rely on emergency services and inpatient care more frequently, resulting in a high number of unplanned and sometimes avoidable hospital admissions [4, 5]. On average, every care dependent person in Germany is hospitalized twice a year [2]. Particularly among older care recipients with cognitive impairments, this exacerbates prognosis dramatically, leading to increased mortality, longer hospital stays, and a higher risk of rehospitalization [6–9]. Furthermore, the transfer from home to the hospital can facilitate significant psychological distress for those affected, known as relocation stress or transfer trauma [10, 11].

Previous studies have shown that at least 30 percent of multimorbid care recipients in emergency departments would not require inpatient therapy if health changes were detected early on and timely medical assessment and treatment, for instance through telemedicine, could be arranged [12, 13]. Furthermore, interdisciplinary coordination of healthcare measures is beneficial for health outcomes.

###  Objective

The aim of the intervention is to provide continuous, needs-based, trans-sectoral and flexible healthcare for individuals receiving care at home during episodes of illness and health crises. Within the trans-sectoral care network established for this purpose, a new digital technology is intended to enable the rapid detection and communication of deteriorations in health status and facilitate early intervention in the home environment. The aim of this study is to assess whether the implementation of a telemedical supported trans-sectoral collaboration network can lead to a reduction in emergency situations and unplanned hospital admissions, improve state of health, quality of life, and care needs of individuals compared to standard care, and to evaluate the enhancement of interdisciplinary cooperation and usability facilitated by the new technology.

##  Methods

###  Design

This is a prospective non-randomized complex intervention study with a pragmatic approach [14, 15]. Important protocol modifications are decided within the project consortium, then submitted to the project sponsor. Subsequently, changes to the German Clinical Trials Register entry will be made.

###  Intervention

The new form of healthcare Stay@Home – Treat@Home (STH) focuses on establishing an interdisciplinary and trans-sectoral network for low-threshold outpatient care in the home of care dependent individuals. This is facilitated through the digital interactive health diary, a telemedical application. Here, information about the participants' health status is collected by themselves, their caregivers, their general practitioner, and all stakeholders involved in acute care within the new form of healthcare and is accessible by them when needed [16]. The new form of healthcare covers two areas of care: primary care as well as acute and emergency care.

The primary care takes place as long as participants are in a stable health condition without acute care needs. Their health status is regularly recorded and reviewed by themselves, their caregivers, and their primary care physician within the digital interactive health diary.

Acute and emergency care comes into play when regular entries in the digital interactive health diary enable the early detection of deteriorating health conditions. Initially, participants or their caregivers contact their general practitioner (GP), who then provides care to the participants as part of standard care. If the general practitioner is unreachable, participants call the medical on-call service of the Berlin Association of Statutory Health Insurance Physicians (KV Berlin) using a special hotline stored in the digital interactive health diary, thereby activating the care network. This triggers an STH event. The medical on-call service center determines the current care needs based on the symptoms of the patient/participant as well as their entries in the digital interactive health diary using the Structured Initial Medical Assessment in Germany (SmED) [17]. The care pathways are outlined in Fig. 1.

**Fig. 1 Fig1:**
[figure not shown]
Care pathways of the new form of healthcare (simplified representation). STH event: event within the new form of healthcare; KV: Association of Statutory Health Insurance Physicians

If immediate medical intervention is required, an emergency is triggered, the emergency medical services are alerted, and the STH event is terminated. If the case is not an emergency, and it is clearly determined that measure 1 or 2 is required, the event is passed on to the telemedical assistance at the Charité. Otherwise, the medical on-call service of the association contacts the association's consulting physician, who then decides on further care for the participants. There are three possibilities: transfer of the case to standard care with simultaneous termination of the STH event (emergency use or referral to the hospital; light grey boxes in Fig. 1); closing of the case, as no acute assistance is necessary (white box in Fig. 1); or an intervention within the framework of the new form of healthcare (dark grey boxes in Fig. 1). Three types of interventions in the participants' home environment are provided: Measure 1 contains a general assistance provided by a nursing aid service without any further medical or nursing assistance. Measure 2 consists of nursing intervention offered by a nursing aid service or the participants' home care service. Measure 3 entails medical intervention facilitated by the medical on-call service, potentially combined with monitoring by a nursing aid service or remote treatment through the telemedical assistance.

While the consulting physician directly assigns the task for measure 3 to the mobile medical on-call service of the association, measures 1 and 2 are controlled via the telemedical assistance, to which the consulting physician assigns the case. Additionally, during an STH event, the telemedical assistance can be utilized by all involved care providers at any time for consultative and coordinating activities. All stakeholders can also access information about the participants' health status in the digital interactive health diary, and all care steps are recorded by the stakeholders in the digital interactive health diary. Every STH event is reviewed and acknowledged by the participants' general practitioner, enabling therapy adjustments for the patients in the primary care setting, if necessary.

Adherence will be also encouraged through regular communication and guidance by the general practitioners as part of the study protocol. There will be no formal follow-up conducted after the intervention. However, reasons for participant discontinuation will be systematically collected to understand the factors influencing dropout rates.

###  Participants

 Assuming that the hospitalization rate in the patient group before the intervention is approximately 20 percent [2] with a potential of reduction to 15 percent during intervention (a reduction of 25 percent), with a power of 90 percent and a significance level of 0.05, the calculated sample size is 1,210 patients for the intervention group [18]. To address sample attrition due to heightened mortality in the research group as well as other unforeseeable drop-outs, about 25 percent additional patients should be recruited, resulting in a total sample size of *n* = 1,500 participants in the intervention group, with at least the same number of controls to be drawn. GPs will be recruited through outreach by the KV, which in turn will recruit eligible participants for the study. Alternatively, the participants will be recruited by a study physician to relieve the GPs. The informed consent will be obtained from the participants by either their GP or the study physician. The intervention group will be derived from eligible insurees of the participating health insurance companies, who are 60 years or older, reside in Berlin in their own home, receive support from a caregiver, and have been either officially granted “care level” 1 or higher, have applied for it or been assessed by their GP as needing “care level” 1 or higher. In Germany, five “care levels” represent a scale used to classify the level of care needed by individuals requiring long-term care. The respective care level determines the subsidies those individuals receive through their nursing care insurance provider. Participants can withdraw their consent to participate in the study anytime. If participants stop meeting the inclusion criteria listed above at some point, e.g. leave their participating insurance company, they will be excluded from the study.

For the control group from the health insurance data (control group 1), insured individuals with similar characteristics to those in the intervention group will be identified from the enrollee and billing data of the participating health insurance companies. For better comparability, the aim is for the control group to also originate from Berlin, Germany. However, if the numbers are not sufficient, patients from structurally similar settlement areas will be included in the control group. A minimum 1:1 matching is planned, ensuring that the control group will be the same size as the intervention group. Depending on the number of insured individuals in the participating health insurance companies, a 1:n matching may also be performed, thereby increasing the size of the control group accordingly.

The control group for the secondary outcomes (control group 2) will be *n* = 300.

The rationale of this study is to select control groups that do not receive the intervention and an intervention group that does. It is based on the study's objective to assess the efficacy of the intervention in comparison to no treatment. For the control group 2 individuals with similar characteristics to those in the intervention group, but being insured by other than the participating health insurance companies, will be included in the study. This design allows it to determine the direct impact of the intervention by observing differences between the groups. The use of two no-intervention control groups is ethically justifiable in this context, as the expected benefits of the intervention are hypothesized but not yet established. This approach ensures that any observed effects can be attributed specifically to the intervention, thereby providing clear insights into its potential benefits.

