**Health insurance perspective**			
Utilization: Hospital stays and emergency responses	Number of hospital stays/ emergency responses	Claims data	primary
Utilization: Ambulatory-care sensitive hospital stays and emergency responses	Ambulatory-care sensitive diagnoses	Claims data	primary
Utilization: ambulatory resource allocation	Ambulatory medical utilization	Claims data	secondary
Cost: New form of healthcare	All costs directed towards the new form of healthcare	Diary and claims data	primary
Cost: Comparison of new form of healthcare versus standard care	Comparison with saved costs of standard care	Diary and claims data	primary

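### The 90% power belongs to a 20% versus 15% comparison with no time window; it is not established for the primary outcome, which is a count, and the 20% is not reconciled with two stays per person-year from the same reference

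*Protocol article*

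**What the plan says.** Methods, Participants, takes as its baseline that "the hospitalization rate in the patient group before the intervention is approximately 20 percent [2". It supposes that the programme could bring this down to 15%, a relative fall of one quarter, and sets 90% power and alpha 0.05. The outcome of the calculation is given as follows: "the calculated sample size is 1,210 patients for the intervention group [18". Controls are to be at least as numerous. An allowance for attrition raises the target to 1,500. No period is attached to either percentage.

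The Background cites the same reference for a different figure: "On average, every care dependent person in Germany is hospitalized twice a year [2".

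Table 1 operationalizes the primary utilization outcome as "Number of hospital stays/ emergency responses". The text on the health insurance perspective also treats the number of stays and the number of treatments as the primary domain. No primary endpoint of any hospitalization (yes/no) is defined.

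Study period gives late entrants at least six months in the programme. By the dates in Trial status (recruitment 25 March 2024 to 30 June 2025, observation to 31 December 2025), individual exposure runs from 6 to about 21 months. The Analysis section leaves the regression model open.

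**The concern.** A sample size holds for an endpoint, a time window and a baseline. Here the calculation uses a proportion, while the outcome to be analysed is a count with unequal exposure. A share of patients hospitalized cannot be interpreted without a window when exposure varies more than threefold. The one figure in the article that does carry a time unit, two stays per person-year, comes from the same reference and points to a much higher share of patients with a stay over any window the study uses.

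At stake are the recruitment target and the 90% power statement. Trial status reports 36 participants enrolled by 17 November 2024 against a target of 1,500 by mid-2025. How many patients the primary outcome really needs is therefore a live question.

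**Working it through.** **1. The plan's own figure.** Inputs: 0.20, 0.15, 90% power, alpha 0.05, 1:1. The article does not state sidedness.
- Unpooled, two-sided: n = (1.960 + 1.2816)² × (0.20×0.80 + 0.15×0.85) / 0.05² = 10.507 × 0.2875 / 0.0025 = 1,208.4.
- Pooled variance under the null: 1,211.5.
- Power at 1,210 per group: 0.8996.
- One-sided, pooled: 988.

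The stated 1,210 is thus a two-sided test of two independent proportions, and its arithmetic is correct.

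**2. What two stays per year implies.** With mean μ = 2t over t years and negative-binomial dispersion k, P(at least one stay) = 1 − (1 + kμ)^(−1/k), or 1 − e^(−μ) for k = 0. The documents give no k, so it is an assumption.

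| Window | k = 0 | k = 1 | k = 2 |
|---|---|---|---|
| 6 months | 63% | 50% | 42% |
| 12 months | 86% | 67% | 55% |

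To bring the share down to 20%, k would have to be about 6.5 for a quarter, 11 for six months or 16 for a year.

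**3. Sample size for the count.** Per group, n = 10.507 × [1/μ₀ + 1/μ₁ + 2k] / (ln RR)². For RR = 0.75, (ln RR)² = 0.08276, so the multiplier is 126.96.

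*(a) Two stays per year, RR 0.75.*
- Six months (μ₀ = 1, μ₁ = 0.75): k = 1 gives 126.96 × 4.333, so 551; k = 2 gives 126.96 × 6.333, so 805.
- Twelve months (μ₀ = 2, μ₁ = 1.5): k = 1 gives 126.96 × 3.167, so 403; k = 2 gives 126.96 × 5.167, so 656.
- At 1,210 per group, power falls below 90% only if k exceeds about 3.6 (six months) or 4.2 (twelve months).

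*(b) 20% read as an annual share, RR 0.75.* The rate must be converted under the same k that enters the variance: rate = (0.80^(−k) − 1)/k, which is 0.25 per year at k = 1 and 0.281 at k = 2.
- Twelve months: k = 1 gives 126.96 × (4 + 5.333 + 2), about 1,440; k = 2 gives 126.96 × (3.556 + 4.741 + 4), about 1,560.
- Six months: k = 1 gives 126.96 × 20.667, about 2,620; k = 2 gives 126.96 × 20.593, about 2,610.

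*(c) 20% to 15% read as the one-year effect itself.* Converting 15% in the same way gives 0.176 (k = 1) and 0.192 (k = 2) per year, so RR = 0.706 and 0.683.
- Twelve months: k = 1 gives 10.507 × 11.667 / 0.1213, about 1,010; k = 2 gives 10.507 × 12.763 / 0.1456, about 920.
- Six months' exposure only: about 1,850 (k = 1) and 1,550 (k = 2).

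**The case against.** The strongest reply is that nothing has been miscalculated and nothing strictly contradicted. The 1,210 reproduces. A proportion of 20% and a mean of two per year are different quantities. The Background speaks of care-dependent people in Germany generally, while Participants describes people aged 60 or over in Berlin, at home and with a caregiver, including some who have only applied for a care level. Without the reference, nobody can say whether its two figures refer to different populations, windows or events. All of this stands. What remains is that the article names no population, window or event definition that would reconcile the two, and that the calculation is for an endpoint the trial does not define.

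Three stronger readings are tempting and not supported:
- **That the trial is underpowered, or far oversized.** Under reading (c) with one year's exposure a count analysis keeps the stated power, and under (a) it has more. A shortfall appears under (b), or under (c) with six months' exposure. The documents do not choose among these.
- **That a 20% annual share means 0.22 stays per year in a negative-binomial calculation.** That is the Poisson conversion, and combining it with extra dispersion overstates the need.
- **That 1,500 fails to cover 25% loss.** Participants says "about 25 percent additional patients should be recruited, resulting in a total sample size of" 1,500. That is an inflation of the calculated number (1,210 × 1.25 = 1,512.5, rounded), not a statement that 25% will be lost.

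The article is also condensed, and a fuller derivation may exist. But the figures it prints do not fit the outcome it prints, and leaving the choice of regression model open does not mend that.

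**Conclusion.** The concern holds in a limited form. The arithmetic behind 1,210 is right for 20% versus 15%, but the 90% power is not established for the number of hospital stays or emergency responses. The baseline has no window and is not reconciled with two stays per person-year from the same reference. The 20% fits that mean only with extreme clustering, or with a different population, window or event definition that is not stated.

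The requirement per group runs from about 400 to about 2,620 across the readings examined, so whether 1,210 is generous or insufficient is undetermined. This range rests on assumed dispersion of 1 to 2, common exposure of 6 or 12 months, 1:1 allocation, a two-sided 5% level, and a rate ratio of 0.75 (0.68 to 0.71 where 20% to 15% is converted directly).

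**What to change.** Reconcile the two figures taken from the reference, stating for each the population, window and event counted. Then restate sample size and power for the count outcome with a negative-binomial rate-ratio calculation. It should use the stay rate and dispersion among comparable insurees from the insurers' pre-period claims, the actual distribution of exposure (6 to about 21 months), and the matching ratio chosen. Report rate, dispersion, exposure, target rate ratio and sidedness beside the result.

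Alternatively, define any hospitalization within a fixed window as a binary primary endpoint. The 1,210 then applies, provided that 20% and 15% are justified for that window.

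The cost is one recalculation and a text change. Study period already provides for claims from eight quarters before entry, so no new data source is needed. The fix does not itself require more patients, although the stated power or target may change.

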###  Data sources

The data for the evaluation will be gathered from two main data sources. Firstly, various reports will be generated from the digital interactive health diary. These reports will encompass health-related basic data entered by participants, their caregivers, and their primary care physicians, such as current condition, diagnoses, therapies, medication plans, level of care needed, allergies, and measured vital parameters. Additionally, questionnaires for process evaluation and evaluation of health and quality of life will be collected via the digital interactive health diary as well as via the online platform SoSci Survey. Furthermore, all data for the STH event will be extracted through digital interactive health diary reports for the evaluation of utilization patterns and costs, as well as for process evaluation.

As a second data source, data from the health insurance companies will be utilized (enrollee data, claims data concerning sick pay, nursing care, short-term care, outpatient and inpatient cases, ambulance services, prescription of medicinal products, medical devices, and aids). This will be used to establish the control group 1 and to obtain data for comparing the new form of healthcare with standard care.

The reports from the diary are continuously accessible in pseudonymized form by the evaluating parties. Each evaluation party receives only the data necessary for their specific research questions. For the evaluation utilization patterns and costs, it is necessary to merge the data from the diary with the enrollee and billing data from the health insurance companies. This is because treatments provided by the mobile medical on-call service within the framework of STH events are partly reimbursed and documented through STH project funds and partly through statutory health insurance.

Data collection forms cannot be provided here. However, all variables and their response formats are described within the protocol.

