###  Analysis

#### Health insurance perspective

Concerning the perspective of health insurance, the control group 1 will be matched through propensity score matching, incorporating sociodemographic variables such as age, gender, level of care dependency, region, as well as morbidity and healthcare utilization in the 12 to 24 months prior to the study commencement. Analyses will focus on differences in the utilization of inpatient and emergency services between the intervention and control groups. Moreover, the study will assess ambulatory-sensitive utilization of inpatient and emergency services. Total costs for the new form of healthcare in addition to costs for standard care will be calculated and compared to the cost savings of standard care. The statistical analyses will be descriptive and inferential, with regression models selected based on data requirements. Additionally, a cost-effectiveness analysis will be conducted.

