#### Patient perspective

For the analyses on the patient level, the development of general health, care dependency and well-being will be evaluated over the period of the study (pre-post-comparison) both descriptively and inferentially. Regression models will be selected based on data requirements. Age, female gender, and lower educational attainment [38] are associated with increased morbidity [39], thus these variables will be included as covariates. The control group 2 follows the same inclusion criteria as the intervention group regarding age, level of care dependency and region.

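### The stated selection rules of the two control groups do not mirror the intervention group's eligibility, so comparability on care need (control group 1) and on caregiver and own-home status (control group 2) is not secured

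*Protocol article*

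**What the plan says.** **Intervention group** (Participants). Eligible insurees are people "who are 60 years or older, reside in Berlin in their own home, receive support from a caregiver". Care need can be shown in three ways: a care level of 1 or higher already granted, or that they "have applied for it or been assessed by their GP as needing" one.

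**Control group 1** (Participants; Data sources; Analysis, Health insurance perspective). Insurees with similar characteristics "will be identified from the enrollee and billing data of the participating health insurance companies". If Berlin does not supply enough, "patients from structurally similar settlement areas will be included in the control group". The insurer data are listed as "enrollee data, claims data concerning sick pay, nursing care, short-term care, outpatient and inpatient cases, ambulance services", followed by prescriptions, devices and aids. Propensity score matching is planned, "incorporating sociodemographic variables such as age, gender, level of care dependency, region, as well as morbidity and healthcare utilization" before the study.

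**Control group 2** (Participants; Analysis, Patient perspective). These are 300 people with similar characteristics "but being insured by other than the participating health insurance companies". The stated rule is: "The control group 2 follows the same inclusion criteria as the intervention group regarding age, level of care dependency and region". They supply the comparison for the survey outcomes, which include the OSSS-3 (social support) and the UCLA Loneliness Scale.

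**The concern.** In a non-randomized comparison, the control group should be one that the treated group's entry rule could have produced. Two of the three routes into the intervention group have no listed counterpart in the data from which control group 1 is built. A participant who enters on a GP's judgement has a known care need and no granted level. A control with no granted level has an unknown care need, and many such insurees may have none. If the matched controls are healthier, their hospital and emergency use is lower, and a real benefit on the primary outcomes is partly hidden.

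For control group 2 the gap is different. Every intervention participant has a caregiver and lives at home. The stated rule does not require either of control group 2. Both features bear directly on support and loneliness, and they may affect how these change over three to six months.

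The Participants section nevertheless says that the choice of control groups lets any observed effect be ascribed specifically to the intervention. The stated rules do not carry that assurance.

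**Working it through.** **1. Criteria side by side**

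| Criterion | Intervention group | Control group 1 | Control group 2 |
|---|---|---|---|
| Care need | granted, applied for, or GP-assessed | level of care dependency as a matching variable | stated to be the same |
| Caregiver support | required | not named in the (open) matching list | not named |
| Own home | required | not named in the (open) matching list | not named |
| Region | Berlin | Berlin, with a fallback | stated to be the same |
| Source | GP or study physician | insurer data | survey recruits |

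GP-assessed need appears in none of the listed insurer items. Application status is not listed either, but enrollee and nursing-care data are, and the article does not say whether these record applications. GP-assessed need is therefore the firmer gap. No rule says how a participant without a granted level is coded for matching.

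**2. The plan's own sample size**

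Inputs (Participants): 20% versus 15%, power 90%, significance level 0.05, taken as two-sided, allocation 1:1.

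n per group = [1.96·√(2·0.175·0.825) + 1.2816·√(0.20·0.80 + 0.15·0.85)]² / 0.05² = (1.0532 + 0.6872)² / 0.0025 ≈ 1,212.

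The plan states 1,210, so the figure reproduces. The planned effect is 5 points, a rate ratio of 0.15/0.20 = 0.75.

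**3. Illustration for control group 1 (inputs assumed; the article gives none)**

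Let s be the share of participants without a granted level. Let d be the gap in underlying hospitalization rate between them and their matched controls that remains after matching. The overall bias is s × d.

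- Smallest case: 5% × 2 points = 0.1 point, which is 2% of the planned 5 points.
- Largest case: 40% × 10 points = 4.0 points, which is 80%.

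Now suppose the true effect is as planned (20% to 15%) and the controls are healthier, so the control rate is 20% − s × d. Power is the normal approximation with 1,210 per group. For a control rate of 19%: [0.04 − 1.96·√(2·0.17·0.83/1,210)] / √((0.19·0.81 + 0.15·0.85)/1,210) = 0.66, giving 75%.

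| s | d (points) | Control rate | Observed ratio | Share of the 25% reduction lost | Power |
|---|---|---|---|---|---|
| 0 | – | 20.0% | 0.75 | 0 | 90% |
| 10% | 5 | 19.5% | 0.77 | 8% | 83% |
| 10% | 10 | 19.0% | 0.79 | 16% | 75% |
| 30% | 5 | 18.5% | 0.81 | 24% | 64% |
| 30% | 10 | 17.0% | 0.88 | 53% | 27% |

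Share lost = (observed ratio − 0.75)/0.25; for example (0.789 − 0.75)/0.25 = 16%.

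The table gives participants without a granted level the same 20% rate as the rest, and it assumes that d survives matching on morbidity and prior use. Either assumption may fail.

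**4. Control group 2**

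No arithmetic applies. The survey outcomes are compared before and after in both groups, at weeks 2–4 and at 3–6 months, with a congruent interval for control group 2. A constant difference in level due to having a caregiver cancels in the change. A difference in trajectory does not: people without a caregiver, or not in their own home, may decline or become isolated at another pace. The first survey also falls after the intervention has begun. The named covariates are age, gender and education, which do not capture caregiver or housing status.

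**The case against.** Much can be said for the plan.

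- **Matching is joint and the list is open.** Controls must resemble participants on morbidity and on 12 to 24 months of prior use as well as on care dependency. That reduces the bias in control group 1, perhaps greatly. This stands, but it cannot be assumed to remove the bias, since new care need may precede heavier use.
- **The diary records the level of care needed** and is merged with insurer data, so participants without a granted level need not be coded as having none. This stands for the intervention group only. Control group 1 has no diary entries, so the variable would then be measured differently in the two groups.
- **Control group 2 shares the care-need criterion.** This stands. Its gap concerns caregiver and own home only.
- **The criteria may simply be condensed.** Control group 2 is to have similar characteristics, and the Limitations section says that only people with a caregiver, or members of participating insurers, can be included. It then describes control group 2 as relaxing the insurer restriction and does not mention relaxing the caregiver one. The text is ambiguous: the criteria are unsecured, not expressly dropped.
- **Selection bias is conceded** in the Limitations section for the intervention group against control group 1. It is conceded in general terms, without the care-need mismatch and without a remedy for it.

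A reader might infer that both contrasts compare different populations, or that the survey contrast favours the intervention on support and loneliness whatever its effect. The documents support neither. Matching narrows the first difference, and the pre-post comparison removes fixed level differences in the second.

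**Conclusion.** The point holds as a gap in comparability, not as proof of bias. For control group 1, the entry rule and the listed data source do not meet for participants without a granted care level. The likely direction is against the intervention, because unmatched care need leaves the controls healthier. The size cannot be derived from the article: under the assumed inputs it runs from negligible (0.1 point) to most of the planned effect (4.0 of 5 points), and it turns mainly on a share the article does not report and on how much the matching achieves.

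For control group 2, the stated rule leaves caregiver support and own-home residence open while support and loneliness are measured. What remains at risk is a difference in trajectory, whose direction and size are unknown.

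It would go too far to say that insurer data cannot identify applications, or that participants without a level will be matched to people with no care need. The article settles neither. An improvement is worth making because it is cheap, and because later modelling cannot recover items that the control data do not hold.

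**What to change.** **Control group 1.** Keep all participants in the primary comparison. Pre-specify a sensitivity analysis restricted to participants with a granted care level of 1 or higher at the index date, matched exactly on care level to controls who also have a granted level. State how participants without a granted level are coded in the propensity score, and report their share.

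**Control group 2.** Apply the caregiver and own-home criteria at screening, or record both in the first survey and adjust for them.

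**Cost.** This needs a little more analysis work and two screening questions. The restricted set is less precise: with an assumed 10% to 30% without a granted level, 1,210 per group becomes 1,210 × 0.90 = 1,089 to 1,210 × 0.70 = 847, and power for 20% versus 15% falls from 90% to about 87% to 77% (same formula as above). That is why the restriction belongs in a sensitivity analysis. As the primary set it would also remove people whom the pragmatic design deliberately includes.

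**Timing.** The sensitivity analysis can be fixed at any time before outcome data are compared. The screening questions need to be in place while control group 2 is being recruited; when the article was submitted, 36 of the planned 1,500 intervention participants had been enrolled.
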